## Criteria for Dose and Schedule Changes

The doses of the investigational drugs will not be changed in this study.

## Discontinuation of Treatment

The administration of an investigational drug is discontinued in the event that the Principal Investigator or another investigator determines that the study cannot be continued for one of the reasons below. The date of discontinuation, the reason, and the course are recorded in the medical record and the Case Report Form (CRF), the necessary tests at the point of discontinuation/dropping out are conducted, and efficacy and safety evaluations are performed.

If the investigational drug is discontinued because of an adverse event, if possible, the patient is followed up until recovery.

1. Notice from the study subject of withdrawal from the study or withdrawal of consent
2. Found not to meet the eligibility criteria after registration
3. Unable to continue study due to adverse event
4. Found to be pregnant
5. Subject unable to attend hospital due to moving house or similar reason
6. Study discontinuation determined to be appropriate by a doctor for any reason other than the discontinuation of the study as a whole

## Concomitant Treatment and Supportive Therapy

The subjects of this study are chronic maintenance hemodialysis patients, and the study is conducted on the basis of continuing treatment for chronic kidney failure and its complications.

## Post-Treatment

There are no stipulations on post-treatment.

1. **Parameters to be Monitored, Tested, and Reported, and Schedule**

## Parameters to be Monitored and Tested and Treatment Information to be Reported

**Consent Obtained – Determination of Eligibility for Study Enrollment**

Subject data: subject ID, age, sex, dialysis history, height, weight, complications, previous medical history, history of current condition, allergies, PS (ECOG), blood pressure, temperature, heart rate, etc.

**Pre-observation Period (1 week)**

The pain score during arteriovenous fistula puncture is measured by VAS (on every occasion dialysis is performed)

Health-related QOL is measured using the SF36 (Acute Version) (after final dialysis)

**Intervention Period I (1 week)**

The pain score during arteriovenous fistula puncture is measured by VAS (on every occasion dialysis is performed)

Health-related QOL is measured using the SF36 (Acute Version) (after final dialysis)

A check is made for drug-induced adverse events such as rash

**Drug Holiday Period (1 week)**

The pain score during arteriovenous fistula puncture is measured by VAS (on every occasion dialysis is performed)

Health-related QOL is measured using the SF36 (Acute Version) (after final dialysis)

A check is made for drug-induced adverse events such as rash

**Intervention Period II (1 week)**

The pain score during arteriovenous fistula puncture is measured by VAS (on every occasion dialysis is performed)

Health-related QOL is measured using the SF36 (acute version) (after final dialysis)

A check is made for drug-induced adverse events such as rash

## 8.2. Schedule for Monitoring, Testing, and Reporting

| Period  Parameter | Consent obtained – determination of eligibility for study enrollment | Pre-observation period (1 week) | Period I (1 week) | Wash out (1 week) | Period II (1 week) |
| --- | --- | --- | --- | --- | --- |
| Explanation of study/obtaining consent | ○ |  |  |  |  |
| Investigation of patient characteristics | ○ |  |  |  |  |
| Examination by doctor | ○ |  |  |  |  |
| Height, weight | ○ |  |  |  |  |
| Temperature, blood pressure, heart rate | ○ | ○ | ○ | ○ | ○ |
| Pain score during arteriovenous fistula puncture measured by VAS (on every occasion dialysis is performed) |  | ○ | ○ | ○ | ○ |
| Health-related QOL measured using the SF36 (acute version) (after final dialysis in that period) |  | ○ | ○ | ○ | ○ |
| Check made for adverse events caused by the interventional drug |  |  | ○ | ○ | ○ |
|  | | | | | |

8.3. Specimen Storage and Use of Specimens by Other Institutions, Etc.

Materials concerning this study stored by the study sites and the Principal Investigator (including records of subject observations, test data, Ethics Committee screening records, and subject consent forms) shall be retained until a date 5 years from the date of completion of the study as a whole or 3 years from the date of final publication of the results of the study, whichever is the later. After the end of the retention period, they are to be disposed of appropriately (shredded or burned).

Specimens such as blood and urine samples will not be collected in this study.

1. **Target Enrollment and Study Period**
   1. Target Enrollment

The target number of applications in this hospital is 20 patients.

The total number of subjects to be enrolled in the study as a whole is 68 patients.

(The study as a whole will include Kanazawa Medical University Hospital, Keiju Medical Center, Anamizu General Hospital, and others)

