## Content of Crossover Study

[figure not shown]

| 介入I期（1週間） | Period I (1 week) |
| --- | --- |
| 介入II期（1週間） | Period II (1 week) |
| 同意取得 | Consent obtained |
| 医薬品使用前検査 | Tests prior to investigational drug use |
| 適格性判断 | Eligibility determination |
| 割付け | Allocation |
| 前観察期（1週間） | Period 0 (measurement of baseline 1) (1 week) |
| 被験医薬品毎透析前 | Test drug use (before each dialysis procedure) |
| 対象医薬品毎透析前 | Control drug use ( before each dialysis procedure) |
| 休薬期間（1週間） | Wash-out period (1 week) |

(1) Written consent is obtained from the subject.

（2） Tests prior to investigational drug use are conducted, and eligibility for enrollment in the study (selection criteria/exclusion criteria) is confirmed.

(3) Subjects determined to be eligible as a result of the tests before investigational drug use are randomly allocated into two groups (Group A and Group B). Those in Group A use the test drug (EMLA) followed by the control drug (Youpatch), and those in Group B use the control drug (Youpatch) followed by the test drug (EMLA).

(4) In Period0 (1 week), pain is evaluated during arteriovenous fistula puncture using a visual analog scale (VAS) on all three occasions dialysis is performed from the start of the week to the weekend (Monday, Wednesday, and Friday or Tuesday, Thursday, and Saturday) without the use of the investigational drugs. The pain score (VAS) during arteriovenous fistula puncture during the final dialysis of that week is defined as the Baseline 1 pain score during arteriovenous fistula puncture (without drug use) [VAS (Group A pre-intervention Period I value) and VAS (Group B pre-intervention Period I value]. Health-related quality of life (QOL) is assessed using the SF36 (Acute Version: 1-week recall period) after the final dialysis of that week (Friday or Saturday).

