## Definition of Adverse Events

An adverse event is any undesirable or unintended injury or its manifestation (including abnormal clinical laboratory test results) that occurs in a study subject, irrespective of whether or not there is a causal relationship with an investigational drug. A side effect (adverse drug reaction, ADR) is an adverse event for which a causal relationship with an investigational drug cannot be excluded (assessed as having a “possible” causal relationship with the investigational drug).

Unexpected ADRs are those ADRs that are not listed on the package insert, or which are listed but for which the nature and severity are not consistent with the description given in the package.

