## Evaluation and Reporting of Adverse Events

Any adverse events occurring within 30 days of the completion of the protocol treatment are to be reported to the Principal Investigator and the Study Coordinator.

The criteria for the severity grading of side effects are 1) Mild: Administration can be continued without treatment; 2) Moderate: Administration can be continued with some sort of treatment; and 3) Severe: Administration should be discontinued or temporarily suspended. Use MedDRA/J (Medical Dictionary for Regulatory Activities/J) for grading adverse events.

The Principal Investigator shall report the state of progress of the study and the occurrence of any adverse events, problems, or other difficulties to the Directors of the study sites once a year.

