## Urgent Reporting and Treatment of Adverse

Follow up adverse events occurring within 30 days of completion of the crossover study until they improve.

- - 1. Urgent Reporting

Should a serious adverse event occur

1. Should a serious adverse event occur, the Principal Investigator or other investigator shall provide appropriate treatment. An investigator shall immediately report this to the Principal Investigator, irrespective of any causal relationship with an investigational drug.
2. The Principal Investigator shall immediately report the serious adverse event concerned to the Director of the study site, and shall notify the supplier of the investigational drug.

Contact for emergency reporting:

Principal Investigator: [name]

Department of Nephrology, Kanazawa Medical University

Address: [name]

[contact] ([name])

[contact]

1. **Cost to Study Subjects and Anticipated Risks and Benefits**

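### The scheduled adverse-event checks seek only drug-caused events and end with Period II, while Section 10 requires all-cause reporting to 30 days after treatment

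*Protocol*

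**What the plan says.** **Reporting rules (Section 10).** Section 10.1 counts an event as adverse "irrespective of whether or not there is a causal relationship with an investigational drug". It keeps the term side effect (ADR) for events where a causal link cannot be excluded. Section 10.2 states: "Any adverse events occurring within 30 days of the completion of the protocol treatment are to be reported", the recipients being the Principal Investigator and the Study Coordinator. Section 10.4 adds: "Follow up adverse events occurring within 30 days of completion of the crossover study until they improve".

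**Scheduled checks (Section 8).** Section 8.1 uses the same sentence for Period I, the drug holiday and Period II: "A check is made for drug-induced adverse events such as rash". The matching row of the Section 8.2 table is "Check made for adverse events caused by the interventional drug", marked under Period I, wash-out and Period II. Period II is the last column of the table.

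**Context.** Section 7.1 gives Group A EMLA then Youpatch and Group B the reverse, with a week free of study drug between the two periods. Section 7.5 makes no stipulations for the time after treatment. Section 14 plans 34 patients per group, 68 in all.

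**The concern.** The two sections differ in two respects.

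- **Scope.** By the protocol's own definitions, Section 8 looks for side effects while Section 10 requires all adverse events. Read literally, the scheduled check asks for an opinion on cause before there is anything to note. Section 15 bases monitoring on what is recorded in the case report forms, so an event left out at this step is unlikely to be found later.
- **Duration.** Section 10 sets a 30-day window, but the schedule plans no contact in it. By checking the wash-out week, the protocol itself treats the week after exposure as worth checking, yet it does so only after Period I.

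At stake is the completeness of the safety record. Section 10.3 lists contact dermatitis, rash, eczema and hyperpigmentation for EMLA, and contact dermatitis, pigment deposition and exfoliation for Youpatch. Any such reaction that first appears after the last application is not actively sought. All the Youpatch reactions are listed with unknown frequency, so an incomplete count loses information that would be useful.

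**Working it through.** **1. The plan's own figure.** The number of exposures rests on the sample size in Section 14. Inputs: difference 10 mm, intra-individual SD 20 mm, two-sided α 5%, power 80%.

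n per sequence = [SD × (z₀.₉₇₅ + z₀.₈₀) / difference]² = [20 × (1.960 + 0.842) / 10]² = 31.4, or 62.8 in total.

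The plan states 31 and 62, which agrees within rounding. Allowing for dropout, 31/0.95 gives 33 and 31/0.90 gives 35. The stated 34 lies between them. No sample-size figure is in dispute here.

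**2. The sections side by side.**

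| | Section 10 (duty) | Section 8 (scheduled check) |
| --- | --- | --- |
| Which events | Any, irrespective of cause | Drug-caused only |
| Until when | 30 days after completion | Period II |

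**3. Treatment weeks followed by a week with a scheduled check.** Each patient has one treatment week on each drug. With 34 per sequence:

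| Drug | Period I weeks (wash-out check follows) | Period II weeks (no check follows) | Share followed by a checked week |
| --- | --- | --- | --- |
| EMLA | 34 (Group A) | 34 (Group B) | 34/68 = 50% |
| Youpatch | 34 (Group B) | 34 (Group A) | 34/68 = 50% |

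With 62 completers, the share is 31/62 = 50%. If minimization gave an unequal split, assumed here to be as far as 30:38 in either direction, the share for a drug would lie between 30/68 = 44% and 38/68 = 56%.

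**4. The 30-day window.** The table has no column after Period II, so no scheduled check falls in the window. At three sessions a week, a patient attends 30 × 3/7 = 12.9, or about 13, dialysis sessions in that time.

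**5. Counting applications instead of weeks.** Each drug has 68 × 3 = 204 applications, 102 in each period. The protocol does not say how often the check is made within a week. If it is made at every dialysis (an assumption), the first two Period II applications in each patient are followed by a later check: 34 × 2 = 68. Then (102 + 68)/204 = 170/204 = 83% of applications have some later check, and the 34 final Period II applications have none. The 50% is therefore a statement about treatment weeks followed by a further checked week.

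**The case against.** The strongest reply is that these are two layers and not a contradiction. Section 8 lists solicited checks, Section 10 adds a wider and longer reporting duty, and a site can comply with both. No passage limits recording to attributed events. Section 10.4 requires serious events to be reported whatever their cause, and Section 15 lists adverse events in general among the matters monitored. Staff also see these patients about 13 times in the 30 days. This much stands: the absence of a scheduled check is not the absence of all ascertainment, and the duty in Section 10.2 remains in force. It does not remove the difference in wording and duration, because the protocol plans no contact through which the wider duty is to be met.

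A reader might also infer more than the protocol supports:

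- **Bias between the drugs.** Each drug comes before the wash-out in one sequence and comes last in the other, so at 34:34 the gap is identical. Follow-up is uneven by period, not by drug.
- **A distorted safety comparison.** The endpoints are VAS and SF-36, and the protocol states no comparison of safety by drug. Tabulation windows may properly be left to a statistical analysis plan.
- **No check on the Period II drug.** Period II has its own check, which can catch reactions to that week's earlier applications. It is also a check for drug-induced events with rash as the example, not a skin check only.
- **Onset date and location not collected.** These are case report form fields, and the form is not shown.

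**Conclusion.** The point holds as a mismatch between Sections 8 and 10 that should be reconciled. The duty covers events of any cause to 30 days; the scheduled checks cover drug-caused events to the end of Period II. Half of the planned treatment weeks on each drug (34 of 68) are followed by a week with a scheduled check, and none of the scheduled checks falls in the 30-day window.

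The likely effect is under-collection of late events and of events not attributed to a drug. How many would be missed cannot be calculated from the protocol. The 50% rests on equal groups and on counting treatment weeks. The efficacy analysis and the sample size are not affected, and the documents give no ground for claiming bias between EMLA and Youpatch. Because safety is not a named endpoint and unscheduled reporting remains possible, this is a worthwhile amendment but not a threat to the trial's main conclusion.

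**What to change.** Reconcile Sections 8.1 and 8.2 with Sections 10.1, 10.2 and 10.4:

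1. Reword the check in 8.1 and in the 8.2 row to *all adverse events, irrespective of cause*, with causality judged after the event is recorded.
2. Add a column after Period II to the 8.2 table, with a check at existing dialysis sessions in the week after Period II and at about day 30. Record any topical anaesthetic used since Period II. The week need not be drug-free: Section 7.5 sets no rule for that time, and this point does not ask for one.

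Treatment weeks followed by a week with a scheduled check would then rise from 34/68 to 68/68 for each drug, and the schedule would reach the end of the 30-day window.

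The cost is an amendment to one table and the matching lines of 8.1, with a few added case report form entries. No visit is added, since patients already attend three times a week. The drawback is that more unrelated events typical of dialysis patients will be recorded and will need a causality assessment. Events in the added checks may also follow use of another topical anaesthetic, which is why that use should be noted.

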## Study Period

Registration period: From approval to December 31, 2018

Date of study termination: December 31, 2019

1. **Evaluation and Reporting of Adverse Events**

## Definition of Adverse Events

An adverse event is any undesirable or unintended injury or its manifestation (including abnormal clinical laboratory test results) that occurs in a study subject, irrespective of whether or not there is a causal relationship with an investigational drug. A side effect (adverse drug reaction, ADR) is an adverse event for which a causal relationship with an investigational drug cannot be excluded (assessed as having a “possible” causal relationship with the investigational drug).

Unexpected ADRs are those ADRs that are not listed on the package insert, or which are listed but for which the nature and severity are not consistent with the description given in the package.

## Evaluation and Reporting of Adverse Events

Any adverse events occurring within 30 days of the completion of the protocol treatment are to be reported to the Principal Investigator and the Study Coordinator.

The criteria for the severity grading of side effects are 1) Mild: Administration can be continued without treatment; 2) Moderate: Administration can be continued with some sort of treatment; and 3) Severe: Administration should be discontinued or temporarily suspended. Use MedDRA/J (Medical Dictionary for Regulatory Activities/J) for grading adverse events.

The Principal Investigator shall report the state of progress of the study and the occurrence of any adverse events, problems, or other difficulties to the Directors of the study sites once a year.

## Expected Adverse Events

Side Effects of EMLA Cream

Major side effects

(1) Shock, anaphylaxis (adverse events observed overseas so frequency unknown)

(2) Impaired consciousness, tremors, convulsions (adverse events observed overseas so frequency unknown)

(3) Methemoglobinemia (adverse event observed overseas so frequency unknown)

Other side effects

|  | ≥10% | 0.1%–10% | Frequency unknown (self-reported overseas) |
| --- | --- | --- | --- |
| Neurological |  | Paresthesia | Dizziness, hypoesthesia, headache |
| Gastroenterological |  |  | Nausea, vomiting |
| Skin | Erythema | Flushing, pallor, induration, pruritis | Vesicles, rash, hives, contact dermatitis, eczema, burning sensation in the skin, skin hyperpigmentation |
| Other |  | Elevated ALT (GPT) | Hematoma, pain, discoloration, swelling, malaise |

Side Effects of Youpatch Tape

Major side effects

Shock, anaphylaxis (frequency unknown)

Other side effects

|  | Frequency unknown |
| --- | --- |
| Hypersensitivity | Reddening, pruritis, contact dermatitis, irritation, hives, sensation of heat |
| Skin | Pigment deposition, skin exfoliation |

## Urgent Reporting and Treatment of Adverse

Follow up adverse events occurring within 30 days of completion of the crossover study until they improve.

- - 1. Urgent Reporting

Should a serious adverse event occur

1. Should a serious adverse event occur, the Principal Investigator or other investigator shall provide appropriate treatment. An investigator shall immediately report this to the Principal Investigator, irrespective of any causal relationship with an investigational drug.
2. The Principal Investigator shall immediately report the serious adverse event concerned to the Director of the study site, and shall notify the supplier of the investigational drug.

Contact for emergency reporting:

Principal Investigator: [name]

Department of Nephrology, Kanazawa Medical University

Address: [name]

[contact] ([name])

[contact]

1. **Cost to Study Subjects and Anticipated Risks and Benefits**

## Cost to Study Subjects and Anticipated Risks

Study subjects may develop side effects of EMLA Cream and Youpatch Tape. If they participate in the study while unaware of an allergy, they may develop allergic reactions such as cutaneous symptoms, mucosal symptoms, respiratory symptoms, gastrointestinal symptoms, neurological symptoms, circulatory symptoms, and anaphylactic shock.

## Anticipated Benefits to Study Subjects

Relief of pain during arteriovenous fistula puncture will improve QOL.

## Overall Assessment and Measures to Minimize Cost and Risk

Study subjects will be carefully selected to exclude those with allergies.

1. **Matters to be Reported to the Directors of Study Sites and Reporting Method**

During this study, the following matters are to be reported to the Directors of the study sites. The reporting method is stipulated by each institution.

## Reporting by Investigators and Subinvestigators

Investigators and subinvestigators shall report the following occurrences to the Directors of the study sites.

- The occurrence of a major concern from the standpoint of respecting the human rights of study subjects and others or concerning the implementation of the study, such as the leakage of data related to the study
- Circumstances or information that threaten the integrity of the conduct of the study or the reliability of the study results, or information that may potentially threaten these.

## Reporting by the Principal Investigator

The Principal Investigator shall report the following matters to the Directors of the study sites, and if necessary, shall consider suspending or terminating the study or amending the Study Protocol.

- Circumstances or information that threaten the ethical validity or the scientific rationality of the study, or information that potentially threaten these, which may affect the continuation of the study
- Circumstances or information that threaten the integrity of the conduct of the study or the reliability of the study results, or information that may potentially threaten these.
- The state of progress of the study
- Occurrences of adverse events associated with the study
- (For invasive studies) The occurrence of a serious adverse event
- Completion of the study (including termination)
- Prepare and submit a Study Completion Report with an overview of the study results
- [For invasive interventional studies (excluding minor invasions)] Final publication of the results
- Management status of human-derived samples and data

1. **Definitions of Endpoints**

## Primary Endpoint

Improvement in pain during arteriovenous fistula puncture before and after drug use (improvement in VAS score)

